
### Sample size

Sample size for the study is based on the primary outcome of change in moderate to vigorous intensity physical activity (min/week) measured by Actigraph accelerometry. Several reviews of web-based physical activity interventions suggest that most studies have small to moderate effects on change in physical activity and have high dropout rates; up to approximately 30 % [6, 8]. Hence, to detect a small to moderate difference in minutes of physical activity per week between groups (video-tailoring, text-tailoring and control), at the study’s primary time point of 3 months, 130 participants per group will be required to achieve 80 % power using an alpha level of 0.05. The number of participants per group has been inflated by 30 % (170 participants per group) to account for drop out. Hence, a total of 510 participants will be recruited into the RCT.

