## Discussion

This study presents an ideal opportunity to study the effectiveness of a specific component within a web-based physical activity intervention. In recent years a growing number of randomized controlled trials have examined the effects of web-based health behavior change interventions [6, 8]. However, these interventions usually have a plethora of different intervention components making it impossible to attribute effectiveness to specific elements within the intervention [62]. Without more knowledge of what components do and do not work, it will be difficult to make progress and improve intervention effectiveness. Previous studies have emphasized the need for research examining the effectiveness of intervention components in isolation [63], and this is what our study will do. As such, we expect that the findings from this study will provide increased understanding of the benefits of new web-based technologies. It is anticipated that the personalized videos will be more engaging compared to personalized text-based information, which will lead to higher overall participant engagement and retention into the intervention. Higher participant engagement has shown to result in higher levels of behavior change [64] and ultimately this will lead to improved health outcomes. Strengths of our study are the use of objective measures to assess physical activity outcomes and web-usage outcomes, a large sample size with sufficient analytical power, a standardized exposure and contact across groups, no face-to-face contact with participants which better mimics real implementation of web-based interventions, and numerous measures to assess secondary outcomes, such as for example: ‘how do environmental attributes moderate intervention effectiveness?’.

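### The dropout allowance multiplies by 1.3 instead of dividing by 0.7, so 510 participants keep 130 per group only up to 23.5 % dropout, not the 30 % cited

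*Protocol article*

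**What the plan says.** The calculation is in the Sample size section of the protocol article. It reports that web-based physical activity studies "have high dropout rates; up to approximately 30" %. The aim is "to detect a small to moderate difference in minutes of physical activity per week between groups", with 3 months as the primary time point, and for this "130 participants per group will be required to achieve 80" % power, "using an alpha level of 0.05". It continues: "The number of participants per group has been inflated by 30" %, to 170, and names dropout as the reason. Hence "a total of 510 participants will be recruited into the RCT".

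No other section gives a different dropout rate or another basis for 170. The Discussion lists among the trial's strengths "a large sample size with sufficient analytical power".

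**The concern.** An allowance for dropout has to leave the required number after the loss. Dropout is a proportion of the people enrolled, so the required number should be divided by the proportion expected to remain. Adding 30 % of the required number gives too few, because the 30 % loss is then taken from the larger, enrolled number.

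What is at stake is whether the stated power belongs to the stated sample size. The Background presents adequate power as a reason for running the trial after underpowered pilot studies, and the Discussion returns to it. The 80 % should therefore hold under the dropout rate cited in the same paragraph, or its limit should be stated.

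**Working it through.** **Inputs, all from the Sample size section:** 130 per group required; 80 % power; alpha 0.05; dropout up to about 30 %; inflation of 30 %; 170 per group; 510 in total. No effect size, standard deviation, sidedness or test is given.

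**1. Reproducing the plan's figure.**
- n × (1 + d) = 130 × 1.3 = 169, rounded to 170; 3 × 170 = 510. This reproduces the plan.
- n / (1 − d) = 130 / 0.7 = 185.7, or 186. This does not reproduce 170.

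The allowance was therefore made by multiplication.

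**2. What 170 leaves at 30 % dropout.**
- 170 × 0.7 = 119 per group; 3 × 119 = 357 in total.
- Shortfall: 130 − 119 = 11 per group, or 33 in total.

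**3. How much dropout 170 does cover.**
- 1 − 130/170 = 0.235, or 23.5 %.

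**4. What full cover at 30 % would need.**
- 186 per group; 3 × 186 = 558 in total, which is 48 more than 510.

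Steps 1 to 4 need no assumption beyond the document.

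**5. Effect on power.** The effect has to be inferred from the plan's own 130 per group and 80 %. Assuming a two-sided two-sample comparison at 0.05:
- Normal approximation: d = √(2/130) × (1.960 + 0.842) = 0.347. With the t-test, d = 0.349.
- Power at 119 per group for that effect: Φ(0.3475 × √(119/2) − 1.960) = Φ(0.720) = 76.4 %. The t-test also gives 76.4 %.
- Effect detectable with 80 % power at 119 per group (t-test): d = 0.365, against 0.349 at 130, a rise of about 4.6 % (0.365/0.349 = 1.046).

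**6. Sensitivity to the assumed test.** In each row the effect is solved again so that 130 per group gives 80 %.

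| Basis | Power at 119 per group |
|---|---|
| Two-sided 0.05, two-sample | 76.4 % |
| One-sided 0.05, two-sample | 76.9 % |
| Two-sided 0.05/3, two-sample | 75.9 % |
| Three-group F-test (f = 0.158) | 76.1 % |

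The loss is 3 to 4 percentage points on every basis.

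**The case against.** The strongest objection is that 30 % is a ceiling reported for other studies and not a forecast for this trial. The section says that the numbers were raised by 30 %, which is literally true, and it never says that 130 remain after a 30 % loss. If dropout is 23.5 % or less, the plan holds as written. This stands as a limit on the point: the allowance fails at the upper figure cited, not at every plausible rate. It does not remove the error. Thirty per cent is the only rate given and the evident source of the inflation, and nothing tells the reader that the protection ends at 23.5 %.

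A second objection is that the planned mixed model uses incomplete records. Everyone randomised has valid baseline accelerometry, and someone who misses 3 months but returns at 9 months still contributes. So 119 is best described as the number with 3-month data, not the number analysed. But the sample size takes no credit for partial records, and the Statistical Analyses section leaves the handling of missing data open.

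A reader might also infer that the Discussion's claim of sufficient power is false, or that a null result at 3 months would be over-read. The documents support neither. The Discussion's claim is qualitative and names no percentage, and power of about 76 % at the upper end of the cited dropout does not refute it. Detectable effects of 0.349 and 0.365 both fit the plan's verbal target, so the reading of a null result would barely change.

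**Conclusion.** The point holds as a minor correction. The allowance was computed as 130 × 1.3, and it secures the required 130 per group only up to 23.5 % dropout at 3 months. At the cited upper rate of 30 %, about 119 per group would have 3-month data, 11 fewer than required.

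That shortfall follows from the document's own numbers. The power figure, about 76 % instead of 80 %, rests on more: an effect inferred from 130 per group and 80 % power (d of about 0.35), an assumed two-sided two-sample test, and no credit for partial data in the mixed model. The other tests tried give 75.9 % to 76.9 %, so the choice of test matters little.

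**What to change.** Keep 510 and correct the statement in the Sample size section in one of two ways:
- say that 80 % power holds provided no more than 23.5 % of participants are lost by 3 months; or
- say that at 30 % dropout about 119 per group would have 3-month data, with power of about 76 % for the effect the plan was sized on (80 % power for d of about 0.365).

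For the second option, the sponsor should put in the value obtained from the effect size actually used, since 76 % is derived here from an implied one. Qualify the power claim in the Discussion to match.

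The cost is wording only: no change to recruitment, design or analysis, and a slightly less favourable power statement. Raising the target to 558 would restore full cover at 30 % dropout, but a loss of this size does not require it.

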### Statistical Analyses

Generalized Linear Mixed Models (GLMM) will be used to analyse the data. GLMM analyses examine changes from baseline to each follow-up time point for each intervention group compared to the control group while accounting for within-person nesting of variables across time [60]. Data will be tested for linearity and normality to ensure the proper statistical techniques are applied. The most appropriate approach to handling missing data will be applied depending on the pattern and amount of the missing data. Linear regression and generalised linear models will be used to analyse moderating and mediating effects of intervention effectiveness, within the limitations of our sample size [61].

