## Abstract

**Background:**

Physical inactivity levels are unacceptably high and effective interventions that can increase physical activity in large populations at low cost are urgently needed. Web-based interventions that use computer-tailoring have shown to be effective, though people tend to ‘skim’ and ‘scan’ text on the Internet rather than thoroughly read it. The use of online videos is, however, popular and engaging. Therefore, the aim of this 3-group randomised controlled trial is to examine whether a web-based physical activity intervention that provides personally-tailored videos is more effective when compared with traditional personally-tailored text-based intervention and a control group.

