### Study Design

This is a three group randomised controlled trial with assessments at baseline, 3 months and 9 months (see Fig. 1). The same website will be used for all groups, but it will be programmed so that it only provides participants with access to the intervention features related to their allocated group. All groups will gain access to a static text-based library that contains generic physical activity information. The control group will only receive access to this library and will not have access to any other intervention features. Findings from previous studies indicate that static websites providing generic information are not effective in increasing physical activity, and can thus act as a control intervention [28]. In addition to having access to the generic library of articles, the ‘text-tailored’ group will have access to eight personally-tailored physical activity sessions that are delivered as personalised text on a webpage over a three-month period. The ‘video-tailored’ group will receive the same eight personally-tailored physical activity sessions, however they will be delivered as personalised videos. The videos will be released at the same schedule as the tailored text in the text-tailored group. All groups will receive regular reminders to return to the website at an identical schedule to control for the amount of contact between groups. This study is specifically designed to isolate the effect of video-tailoring and compare it with a text-tailored group and a control group. Using the same web-based platform for all groups ensures that website usage between groups is not confounded by non-specific website elements such as design, readability, usability and user-friendliness, as these may differ when using different websites and influence actual usage [29]. Having a web-based control group ensures that exposure to intervention contents across all groups can be objectively measured through website-usage statistics.

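### The analysis section names contrasts with control but no direct video-versus-text contrast, although comparing video with text is a stated aim

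*Protocol article*

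**What the plan says.** Four places in the protocol article bear on this point.

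- **Abstract, Background.** The aim is to find out whether an intervention that "provides personally-tailored videos is more effective when compared with traditional personally-tailored text-based intervention and a control group". The last paragraph of the main Background section repeats both comparators.
- **Study Design.** "This study is specifically designed to isolate the effect of video-tailoring and compare it with a text-tailored group and a control group". The two tailored groups share platform, content, release schedule and reminders, and differ in delivery format.
- **Sample size.** The trial is sized "to detect a small to moderate difference in minutes of physical activity per week between groups (video-tailoring, text-tailoring and control"), at the primary time point of 3 months. No pair of groups is singled out.
- **Statistical Analyses.** "GLMM analyses examine changes from baseline to each follow-up time point for each intervention group compared to the control group". This is the only sentence in the section that says which groups are compared.

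**The concern.** The contrast that isolates video is video against text. Video against control mixes the medium with everything else that the control group lacks: tailoring, eight sessions and action plans. Yet the analysis section lists the two contrasts with control and leaves out the one between the tailored groups.

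An analyst who follows that section would report two effects against control. Neither tests whether video does better than text. A reader who still wants an answer may compare the two p-values, and a difference in significance is not a test of a difference. A video-text contrast added after the results are known would not be prespecified.

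**Working it through.** **1. Needed against named contrasts (primary outcome)**

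| Contrast | Needed for the aim? | Named in Statistical Analyses? |
|---|---|---|
| Video − control | yes | yes |
| Text − control | supporting | yes |
| Video − text | yes | no |

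The mismatch is established by the text alone. The steps below only size it.

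**2. The plan's own figure.** The article states that "130 participants per group will be required to achieve 80 % power using an alpha level of 0.05". It gives no numerical effect or SD, so 130 cannot be derived from its inputs, only solved backwards. For two means with SD = 1 and a two-sided test:

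d = (1.960 + 0.842) × √(2/130) = 0.347.

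So 130 per group fits d of about 0.35, if the test is two-sided (sidedness is not stated). I use d = 0.20, 0.35 and 0.50 to span "small to moderate difference in minutes of physical activity per week". For n I use the stated 130, and 119, which is what remains of 170 after the article's 30 % dropout (170 × 0.70).

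**3. Reading video's advantage from two tests against control.** Assume video and text are truly equal, each d above control. Each test statistic has mean d × √(n/2). The two statistics have correlation 0.5, because the groups are equal in size and share one control. Then

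P(video only) = P(video significant) − P(both significant).

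The figures below come from the bivariate normal distribution, counting results in the beneficial direction at the two-sided 5 % level.

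| d | n per group | P(video significant) | P(both) | P(video only) |
|---|---|---|---|---|
| 0.20 | 119 | 0.338 | 0.187 | 0.151 |
| 0.20 | 130 | 0.364 | 0.208 | 0.156 |
| 0.35 | 119 | 0.770 | 0.647 | 0.123 |
| 0.35 | 130 | 0.806 | 0.695 | 0.111 |
| 0.50 | 119 | 0.971 | 0.948 | 0.023 |
| 0.50 | 130 | 0.981 | 0.965 | 0.016 |

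By symmetry, exactly one of the two tests is significant twice as often, for example 2 × 0.111 = 22 % at d = 0.35 and n = 130. A direct two-sided 5 % test of video against text favours video wrongly in 2.5 %. The excess is therefore four- to sixfold at d = 0.20 to 0.35 and is gone at d = 0.50.

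**4. What the direct contrast can deliver.** It has the same precision as either contrast with control. At 130 per group and two-sided 0.05, power is:

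| True video − text difference (d) | Power |
|---|---|
| 0.20 | 36 % |
| 0.25 | 52 % |
| 0.30 | 68 % |
| 0.35 | 81 % |
| 0.50 | 98 % |

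If text delivered half of a 0.35 video effect, the difference would be 0.175 and power 29 %. Naming the contrast does not change that power, but it is why the CI should be reported whatever the p-value.

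**5. Alpha.** With 0.05/3 = 0.0167 for each of three contrasts, the critical value is 2.394. At 130 per group the detectable d rises to (2.394 + 0.842) × √(2/130) = 0.40, and power at d = 0.35 falls from 81 % to 67 %.

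**The case against.** The strongest reply is that this is incomplete drafting in a condensed article. The analysis sentence does not say 'only', and it reads partly as a general description of what the model does. The aim, the design section and the sample-size phrase "between groups (video-tailoring, text-tailoring and control") all point to an intended comparison with text, and a full SAP may list it. A three-group model yields video minus text from the same fit; its point estimate is simply the difference between the two effects against control.

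Much of this stands. It rules out some stronger readings that a reader might infer:

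- *That the trial cannot test video against text, or that the comparison was deliberately dropped.* The documents do not support this. The randomisation, data and model all allow it, and three sections announce it.
- *That the investigators will judge video by comparing two p-values.* The article says this nowhere. The error rates above show what would follow from such a reading; they do not describe a planned procedure.
- *That the false-conclusion rate is a fixed figure.* It depends on an assumed d, and at d = 0.50 it is no worse than the direct test.
- *That the title promises a comparison with text.* The title mentions only tailored videos.

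The reply does not remove the point. Silence on contrasts could be left to a SAP, but this section does name its contrasts, and they do not match the aim. The sample-size phrase picks no pair and sets no test. Nor can the missing CI be built safely from the two reported effects, because they share a control group. Treating them as independent would give a standard error of √(4/n) instead of √(2/n), which is 0.175 instead of 0.124 in SD units at n = 130.

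**Conclusion.** The point holds as a mismatch within the article. Video against text is a stated aim and the comparison that isolates video, and the only analysis section names contrasts with control alone. As written, that aim has no prespecified test or CI on the primary outcome. The design and data are sound.

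The size of the risk is conditional. It assumes that someone falls back on the indirect reading, that video and text are equally effective, and that tests are two-sided at 0.05 with 119 to 130 per group. Under those assumptions a spurious advantage for video appears in about 15–16 % of trials at d = 0.20, 11–12 % at d = 0.35 and about 2 % at d = 0.50, against 2.5 % for a direct test. The finding itself needs none of these figures.

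**What to change.** In Statistical Analyses:

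1. Name the video-minus-text contrast in change in accelerometer-measured moderate-to-vigorous activity (min/week) at 3 months, from the same GLMM, as a prespecified contrast alongside the two with control, reported with its 95 % CI.
2. State that any claim that video is better than text rests on this contrast, and that a non-significant result is reported through its CI and not as equivalence.
3. State how the 0.05 alpha is handled across the contrasts, for example by a fixed testing order.

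The cost is a few sentences and one more contrast from a model already being fitted; no new data are needed. The downside lies in item 3. An equal split over three contrasts lowers power at d = 0.35 and 130 per group from about 81 % to 67 %. A fixed order tests each contrast at the full 0.05, but later contrasts are tested only if the earlier ones succeed, so the order has to be chosen in advance.

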### Procedure

When contact details of eligible people are received through the website, a project officer will make contact either through e-mail or phone (according to indicated preference) to verify the information provided. Subsequently, people will receive an Actigraph activity monitor using registered mail, as well as instructions on how to use the device, an Actigraph monitor log, a participant information sheet, and a return post-bag. They will be asked to wear the activity monitor for 7 consecutive days (and nights if comfortable) from the day of receipt. A project officer will contact potential participants to ensure the activity monitor has arrived and that they are wearing the device as instructed. At this time, the project officer will also schedule a time to conduct the self-reported baseline measures. The self-reported baseline measures will be administered via Computer Assisted Telephone Interviewing (CATI) by trained interviewers who are blinded to group allocation from the Population Research Laboratory (PRL) at the Central Queensland University (CQU). The CATI assessment will take approximately 30 minutes to be completed. When the activity monitor with valid data and Actigraph log sheet are returned to the university and the CATI assessment has been completed, participants will be randomised into one of three groups using a randomly generated sequence through freely available software (www.randomization.com). The same measurement procedures will be repeated at 3 and 9 months. These study procedures ensure the collection of high quality data without face-to-face contact. This better represents the reality of using health promotion websites and allows that participants can live anywhere in Australia.

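### Primary GLMM: specify a common baseline mean or a baseline MVPA covariate, which gains precision at no cost over an ordinary group-by-time contrast

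*Protocol article*

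**What the plan says.** The Sample size section of the Protocol article bases the trial on "the primary outcome of change in moderate to vigorous intensity physical activity (min/week) measured by Actigraph accelerometry", assessed "at the study’s primary time point of 3 months". The Statistical Analyses section names generalized linear mixed models and states that "GLMM analyses examine changes from baseline to each follow-up time point", comparing each intervention group with control and allowing for correlation within persons over time. It does not say whether baseline is a response with its own mean in each group, a response with one mean shared by all groups, or a covariate.

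On the availability of baseline data the article is clear. The Procedure section allows randomisation only "When the activity monitor with valid data and Actigraph log sheet are returned to the university" and the telephone interview is done. The Measures section excludes anyone who refuses the baseline monitor or repeatedly returns invalid data.

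**The concern.** The natural reading of these sections is a repeated-measures model with three visits, where the effect is the group-by-time contrast from baseline to 3 months. If each group has a free baseline mean, that contrast subtracts an estimated baseline difference which randomisation has already made zero in expectation. Chance imbalance at baseline then enters the estimate as noise. Every randomised participant has a pre-randomisation MVPA value, so the known equality can be used at no cost. What is at stake is the standard error of the primary comparison, and so its power.

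**Working it through.** **Inputs from the Protocol article, Sample size section**
- Sample size and power: "130 participants per group will be required to achieve 80 % power".
- Significance level: "using an alpha level of 0.05". Sidedness is not stated; two-sided is assumed.
- Effect: verbal only, "to detect a small to moderate difference in minutes of physical activity per week between groups". No difference in min/week, SD or standardised effect is given.

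**Inputs not in the document, hence assumed:** rho (baseline to 3 months) from 0.5 to 0.9; equal SD at both visits; complete data; Gaussian model with identity link.

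**Step 1. The plan's own figure.** The 130 cannot be reproduced directly because the effect has no number. Back-solving for a pairwise comparison:

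d = √(2/130) × (1.960 + 0.842) = 0.347 in units of the SD of change (0.349 with the t distribution).

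Conversely, d = 0.35 gives 129 per group, so 130 is plausible.

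**Step 2. Variance of the 3-month contrast, n per group**
- Free baseline means: (2/n) × 2σ²(1 − rho), the same as an unadjusted change-score comparison.
- Common baseline mean, or baseline covariate: (2/n) × σ²(1 − rho²).
- Ratio v = (1 − rho²) / [2(1 − rho)] = (1 + rho)/2, a reduction of (1 − rho)/2.

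A generalised least squares calculation with three groups, three visits, compound symmetry, σ² = 1 and n = 130 agrees:
- rho 0.5: 0.01538 against 0.01154, ratio 0.75
- rho 0.7: 0.00923 against 0.00785, ratio 0.85
- rho 0.8: 0.00615 against 0.00554, ratio 0.90

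**Step 3. Effect on power and sample size.** The back-solved effect is held fixed. Power at 130 per group is Φ(2.802/√v − 1.960), and n for 80 % power is 130 × v, rounded up.

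| rho | v | Variance cut | SE cut | Power at 130 | n per group for 80 % |
|---|---|---|---|---|---|
| free baseline means | 1.00 | – | – | 80 % | 130 |
| 0.5 | 0.75 | 25 % | 13.4 % | 89.9 % | 98 |
| 0.7 | 0.85 | 15 % | 7.8 % | 86.0 % | 111 |
| 0.8 | 0.90 | 10 % | 5.1 % | 84.0 % | 117 |
| 0.9 | 0.95 | 5 % | 2.5 % | 82.0 % | 124 |

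**Step 4. Unequal spread.** With SD σ0 at baseline and σ1 at follow-up, the per-person variance saved is

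(σ0² + σ1² − 2·rho·σ0σ1) − σ1²(1 − rho²) = (σ0 − rho·σ1)².

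This is never negative, but it vanishes when σ0 = rho·σ1. As an illustration, take σ0 = 0.7 and σ1 = 1:
- rho 0.5: 0.75/0.79 = 0.95
- rho 0.6: 0.64/0.65 = 0.98
- rho 0.7: 0.51/0.51 = 1.00

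The gain is then about 5, 2 and 0 %.

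**The case against.** The strongest objection is that the article does not exclude the better model. A mixed model with a common baseline mean also estimates between-group differences in change from baseline, so the quoted sentence fits it as well as the model criticised. How baseline is parameterised is detail that a one-paragraph analysis section often leaves to an SAP. This stands in part. A reader might infer that the plan has ruled out any baseline constraint or adjustment, but the text neither includes nor excludes one. What remains is that the article itself prints the primary outcome and the contrast as change from baseline, and an analyst following that wording would reach the less efficient model by default.

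A second objection concerns size, and it also stands. Rho and the SDs are not given. The Participants section enrols only people below the activity guideline, which may narrow the baseline spread, although screening is by online questionnaire and any truncation of accelerometer MVPA would be partial. The article also allows for a non-Gaussian analysis after checking normality, and the ratios above do not carry over exactly to that case.

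A reader might also link this point to a shortfall in power: 170 × 0.7 = 119 evaluable per group if 30 % are lost, with about 76 % power for unadjusted change. That shortfall comes from how the sample size was inflated for dropout. It is a separate matter and is not evidence for this point.

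**Conclusion.** The point holds as a recommendation on efficiency. Under the natural group-by-time reading with free baseline means, the primary contrast has the variance of an unadjusted change score, while the design supplies what is needed to do better. Under equal variances, complete data and a Gaussian model, the variance saving is 25 % at rho 0.5 and 5 % at rho 0.9, and it can be close to nil if baseline spread is much narrower than follow-up spread. Apart from a negligible degree of freedom, the alternative does not cost precision.

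A reader might go further and take the planned analysis to be biased or invalid. The documents do not support that: under randomisation the unadjusted contrast in change is unbiased, and only its precision is in question.

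**What to change.** Add a sentence to the analysis plan, before unblinded data are seen, choosing one of two forms:
- a mixed model with one baseline mean common to all groups and group effects only at 3 and 9 months; or
- a model for the follow-up values with baseline MVPA as a covariate.

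Name the resulting 3-month between-group difference as the primary estimate. The outcome can still be described as change, because with baseline as a covariate the group effect is the same whether the response is the follow-up value or the change.

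Apply the same rule to the other outcomes measured at 0, 3 and 9 months. Accelerometer sleep is collected only from those willing to wear the monitor at night, so some baseline values will be missing. There the common-mean form has the advantage of keeping participants who lack a baseline value.

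The cost is wording only: no extra data, recruitment or participant contact. If the sponsor already intends one of these models, the sentence simply settles the ambiguity.
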